#### Serious adverse events

2.7.2

Serious adverse events include the following:

1. Fatal or life-threatening2. The patient needs to be admitted to hospital for treatment or extended hospitalization time3. Resulting in persistent or severe disability/functional impairment4. The subjects’ offspring have congenital anomalies/birth defects5. It is medically important or requires intervention to prevent the occurrence of the above-mentioned conditions.

Once the researcher believes that a serious adverse event has occurred, it should be reported to the sponsor within 24 hours after the occurrence and reported to the ethics committee as soon as possible. The case report form for serious adverse events should record the information related to the event as completely and in detail as possible.

Investigators should evaluate and record serious adverse events in the case report form as follows: severity, relationship to the investigational drug, actions taken regarding the investigational drug, and current outcome.

### Sample size calculation

2.8

This sample size was approximated based on 20% differences between two groups, at 80% detection power.

Calculation method: The primary purpose of this study is to prove that the vaccine treatment group is more effective than the placebo (standard care), with PFS as the main efficacy evaluation index, the planned enrollment time is 24 months, and all subjects are evenly enrolled in the study. The follow-up time is 12 months. According to previous research, it is assumed that the median PFS of the traditional treatment (the control group) is 4 months, and the median PFS of the vaccine group is 10 months (13). The design of crossover of patients who failed in group 1 to group 2 does not affect the statistical results of PFS of the main study. It is based on the PFS before crossover as the statistical calculation.

The 6th month is selected as the interim analysis time node. Considering 0.1 loss to follow-up, 40 patients need to be recruited, with an average of 20 people in each group (**Table 2**). Through the interim analysis, we can make a preliminary validity judgment on the main purpose of this study to determine whether to continue recruiting more patients.

**Table 2 T2:** Sample size calculation for an interim analysis using log rank tests.

Look	Time	–Sample size–		—————Events—————				—Cum.subject time—	
		Group1	Group2	Group1	% of S.S.	Group2	% of S.S.	Group1	Group2
1	6.0	19.2	19.3	6.2	32.1	3.5	18.0	35.6	41.1
2	12.0	38.3	38.5	17.0	44.5	10.4	27.2	98.0	122.8
3	18.0	57.5	57.7	28.7	50.0	18.6	32.2	166.0	217.3
4	24.0	77.0	77.0	40.7	52.9	27.1	35.2	234.9	316.0
5	30.0	77.0	77.0	46.5	60.5	32.3	41.9	268.2	375.1
6	36.0	77.0	77.0	47.7	61.9	33.9	44.0	274.4	393.7

Considering that this study is aimed at pan-tumor and the results of previous studies are based on small samples of liver cancer, we made 4 hypotheticals median PFS prediction values for statistical analysis. The final median PFS was 4 months in the control group and 8 months in the neoantigen vaccine group. The two groups will be enrolled in a 1:1 ratio, α=0.025 (two-sided), β=0.2, and at least 154 subjects with 77 subjects each group are required and the research power reached 80% (**Table 3**).

**Table 3 T3:** Total sample size calculation.

Power	N1	N2	N	Haz ratio (HR)	Ctrl med surv time (M1)	Trt med surv time (M2)	Accrual pat’n	Accrual time/total time	Ctrl loss	Trt loss	Ctrl to trt	Trt to ctrl	Alpha	Beta
0.8028	76	77	153	0.50	4.00	8.00	Equal	24/36	0.10	0.10	0.00	0.00	0.025	0.1972
0.8007	46	47	93	0.40	4.00	10.00	Equal	24/36	0.10	0.10	0.00	0.00	0.025	0.1993
0.8000	481	481	962	0.75	6.00	8.00	Equal	24/36	0.10	0.10	0.00	0.00	0.025	0.2000
0.8003	163	163	326	0.60	6.00	10.00	Equal	24/36	0.10	0.10	0.00	0.00	0.025	0.1997

The sub-group analyses based on high versus low radiation dose are pre-specified exploratory analyses. As there are currently no published studies providing reliable estimates of PFS differences between these sub-groups in the context of neoantigen vaccine therapy, we were unable to perform a dedicated power analysis for the subgroup comparisons. These analyses are intended to be hypothesis-generating and will inform the design of future prospective studies. Additionally, in real-world clinical settings, radiation doses vary considerably among patients, introducing potential confounding effects. To address this, our study design pre-stratified patients into high-dose and low-dose radiation groups rather than allowing radiation prescriptions to vary freely. This approach helps reduce confounding from dose heterogeneity and enhances the interpretability of subgroup findings.

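### The 0.1 loss to follow-up has no time unit, and Tables 2 and 3 reproduce only if it means 10% per month, a rate the article neither states nor justifies

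*Protocol article*

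**What the plan says.** All inputs are in section 2.8 of the protocol article.

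- **Effect:** "The final median PFS was 4 months in the control group and 8 months in the neoantigen vaccine group", a hazard ratio of 0.50.
- **Error rates and size:** "α=0.025 (two-sided), β=0.2, and at least 154 subjects with 77 subjects each group are required and the research power reached 80" per cent. The chosen row of Table 3 shows 76 + 77 = 153 patients and power 0.8028.
- **Allocation:** "The two groups will be enrolled in a 1:1 ratio".
- **Accrual and follow-up:** "the planned enrollment time is 24 months, and all subjects are evenly enrolled in the study", and "The follow-up time is 12 months". Table 3 writes this as 24/36.
- **Loss:** the only prose statement is "Considering 0.1 loss to follow-up, 40 patients need to be recruited, with an average of 20 people in each group". Table 3 gives 0.10 for each arm in all four scenarios. No time unit appears in either place.
- **Projected events:** Table 2, titled "Sample size calculation for an interim analysis using log rank tests", ends at month 36 with 47.7 of 77 events in group 1 (61.9%) and 33.9 of 77 in group 2 (44.0%). Cumulative subject time is 274.4 and 393.7 months.

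**The concern.** With medians of 4 and 8 months and at least 12 months of potential follow-up for everyone, nearly all controls and most vaccine patients should have progressed or died by month 36. Table 2 projects far fewer. A loss of one patient in ten cannot explain the gap, so the software must have used a much heavier loss than a plain reading of the prose suggests.

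Power in a log-rank comparison depends on events. If the loss input is not the intended one, then the event projections, the 80% power and the recruitment target of 154 do not follow from the design described. If it is the intended one, the plan expects to lose nearly half its patients before the primary endpoint and does not say so.

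**Working it through.** **Model.** Exponential PFS with hazard λ, exponential loss with hazard η, uniform accrual over A = 24 months, analysis at T = 36 months. With h = λ + η:

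P(event) = (λ/h) × {1 − [exp(−h(T−A)) − exp(−hT)] / (hA)}

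λ is ln 2/4 = 0.1733 for control and ln 2/8 = 0.0866 for vaccine.

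**Step 1: the stated medians are in Table 2.** Events divided by subject time at month 36 give 47.7/274.4 = 0.174 and 33.9/393.7 = 0.086 per month, which match λ. So the low event counts come from short observed time, not from other medians.

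**Step 2: no loss (η = 0).** P(event) is 0.970 and 0.851, or 74.7 + 65.5 = 140.3 events before rounding. Table 2 has 47.7 + 33.9 = 81.6, about 59 fewer.

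**Step 3: reproduce Table 2 with 10% loss per month**, η = −ln 0.9 = 0.1054.

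- Control: h = 0.2787; 0.6219 × 0.9947 = 0.6186; × 77 = 47.6.
- Vaccine: h = 0.1920; 0.4513 × 0.9785 = 0.4416; × 77 = 34.0.

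| Month | Computed events | Table 2 |
|---|---|---|
| 6 | 6.2 / 3.5 | 6.2 / 3.5 |
| 12 | 17.0 / 10.6 | 17.0 / 10.4 |
| 18 | 28.8 / 18.8 | 28.7 / 18.6 |
| 24 | 40.7 / 27.3 | 40.7 / 27.1 |
| 30 | 46.5 / 32.4 | 46.5 / 32.3 |
| 36 | 47.6 / 34.0 | 47.7 / 33.9 |

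Every cell agrees within 0.2. Subject time at month 36 is 274.9 and 392.4, against 274.4 and 393.7 printed. At 10% per year it would be 412 and 706.

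**Step 4: reproduce Table 3.** Power from a Lakatos log-rank model, two-sided alpha 0.025:

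| Medians (months) | N | Printed power | 10% per month | 10% over 12 to 36 months |
|---|---|---|---|---|
| 4 vs 8 | 153 | 0.8028 | 0.8025 | 0.954–0.961 |
| 4 vs 10 | 93 | 0.8007 | 0.7987 | 0.956–0.962 |
| 6 vs 8 | 962 | 0.8000 | 0.7999 | 0.965–0.971 |
| 6 vs 10 | 326 | 0.8003 | 0.7992 | 0.969–0.975 |

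Reading alpha as one-sided does not rescue another explanation: one-sided 0.025 with monthly loss gives 0.871 for the first row.

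**Step 5: what the monthly rate implies.** Expected losses before progression are the same expression with η/h in place of λ/h: 29.0 control + 41.3 vaccine = 70.3 of 154 (46%). Among patients still event-free, 1 − 0.9^12 = 72% would be lost by 12 months.

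**Step 6: if 10% of patients was meant.** The time over which the loss accrues is not given, so it is an assumption. Power is by Schoenfeld, Φ(√(d/4) × ln 2 − 2.241), with 77 per arm:

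| Loss | Events d | Power at HR 0.5 |
|---|---|---|
| 10% per month | 81.6 | 0.81 |
| 10% by 12 months | 71.4 + 61.2 = 132.6 | 0.96 |
| 10% by 36 months | 73.6 + 64.0 = 137.6 | 0.97 |
| 10% contribute nothing | 0.9 × 140.3 = 126 | 0.95 |

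The Lakatos values for 77 + 77 are 0.955 (12 months) and 0.962 (36 months).

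**Step 7: size for 80% power.** Schoenfeld events = 4 × (2.241 + 0.842)² / (ln 2)² = 79.1, so 80. The corresponding N over the 12 to 36 month range is 90 to 93 by Schoenfeld, 97 to 100 by Freedman and 92 to 96 by Lakatos. Simple inflation of the no-loss Lakatos N gives 90/0.9 = 100. Keeping 154 instead, 80% power is reached at a hazard ratio of about 0.585 to 0.59 with 10% loss per year.

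**The case against.** The strongest reply is that the article never says 10% in total. That is correct. A reader may infer it because it is the plain sense of the prose, but no section says so and Table 3 prints no unit. If the sponsor meant 10% per month, Tables 2 and 3 are arithmetically right and 154 is the correct size. The documents therefore do not support the claim that the printed figures are wrong on every reading. What remains on the monthly reading is an undisclosed and unjustified assumption that 46% of patients are lost before progression.

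The second reply is that the error, if it is one, is on the safe side. This also stands. A reader might infer an underpowered trial or an inflated type I error. The calculation shows the opposite for power, and the choice of loss rate does not alter the alpha of the log-rank test. The cost is possible over-enrolment of about 55 to 65 patients (154 less 90 to 100) and event projections that are too low.

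Third, the sentence about 40 patients concerns the month-6 look. It shows no error by itself: 19.2 + 19.3 is rounded up to 20 per group. It matters only as the sole prose statement of the loss. The evidence is in Table 2's event columns and Table 3's rows.

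This is not detail that can wait for an analysis plan. The inputs and outputs are both printed in section 2.8, and the reader cannot connect them without supplying a rate that is not there.

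**Conclusion.** The point holds in a limited form. The loss input lacks a time unit, and the tables correspond to 10% per month, which the article neither states nor justifies. This part is firm: it rests only on printed figures and reproduces all twelve event cells of Table 2 within 0.2 and all four powers of Table 3 within about 0.002.

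The size of the discrepancy is conditional on what was intended. Taking 0.1 as 10% of patients, with exponential PFS and loss accruing over 12 to 36 months, the design at 154 has about 95% to 96% power by the Lakatos model (96% to 97% by Schoenfeld), not 80%. It would then be over-sized for its stated target. If the monthly rate was intended, the numbers stand and the defect is one of disclosure and justification.

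**What to change.** In section 2.8, state the time unit of the loss rate, re-run Tables 2 and 3 with the intended rate, and give the required number of PFS events (about 80 by Schoenfeld for a hazard ratio of 0.5, two-sided alpha 0.025 and 80% power). Then do one of the following:

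- **If 10% of patients was meant, restate N** at roughly 90 to 100, naming the method and the period over which loss accrues.
- **If 10% of patients was meant and 154 is kept, restate the power** as about 95% to 96% at a hazard ratio of 0.5, or 80% at about 0.585 to 0.59. Label these figures as conditional on the assumed loss.
- **If 10% per month is intended, say so and justify it.** Disclose that about 70 of 154 patients are expected to be censored before progression.

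The cost is a software re-run and a rewritten section. No option adds patients.

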**Figure 1 f1:**
[figure not shown]
Flowchart of the study design.

**Control group:** placebo + conventional treatment (including radiotherapy) group,

**Intervention group:** personalized tumor peptide vaccine + conventional treatment (including radiotherapy) group,

Subjects will be stratified according to different cancer types and first, second, and third-line treatment stages based on individual condition assessment, and then randomly enter two cohorts in a 1:1 ratio. In addition, there is a one-way crossover experiment (cross-over design) during the research process. Cross-over to the investigational treatment arm (peptide vaccine plus radiotherapy) will be permitted only for patients in the control group who demonstrate radiologically confirmed disease progression, as assessed by RECIST 1.1 and verified by the investigator. Eligibility for cross-over requires that patients meet predefined safety and clinical criteria, including an ECOG performance status of ≤2, absence of Grade ≥3 adverse events, and adequate hematologic, hepatic, and renal function. The proportion, timing, and reasons for cross-over will be systematically recorded and transparently reported. The intervention group will undergo the second phase of personalized tumor peptide vaccine group plus conventional treatment (including radiotherapy), and the response rate of the two phases will be evaluated before and after crossover. In both cohorts, all subjects received radiotherapy, and radiotherapy doses will be further divided into low and high doses. This design will allow us to answer questions about vaccination efficacy and the impact of various radiation doses.

For patients who want to enroll in neoantigen clinical trials, screening for neoantigens may be recommended. It is necessary to take the patient’s fresh tumor tissue (surgery or biopsy or cerebrospinal fluid, pleural effusion, ascites, etc.), and perform whole-exome and whole- transcriptome sequencing on peripheral blood for further clinical development of individualized targeted treatment plans. At the same time, these test data can be used for personalized tumor neoantigen screening in this study. Peptide vaccine therapy requires an 8-week preparation period for the preparation of the peptide vaccine, during which patients continue to maintain standard treatment.

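### The month-6 PFS interim that decides whether to keep recruiting rests on about 10 of 82 events, too few to inform that decision

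*Protocol article*

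**What the plan says.** All of the following is in the protocol article.

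- **Timing and size (section 2.8).** "The 6th month is selected as the interim analysis time node", and "40 patients need to be recruited, with an average of 20 people in each group".
- **Use (section 2.8).** From the interim result, "we can make a preliminary validity judgment on the main purpose of this study to determine whether to continue recruiting more patients". The same section gives the primary purpose as showing that the vaccine group does better than control, with PFS as the main measure.
- **Expected events (Table 2).** For look 1 (month 6) the event columns read "6.2 32.1 3.5 18.0", that is 6.2 control and 3.5 vaccine events, with percentages. For look 6 (month 36) they read "47.7 61.9 33.9 44.0". The table labels six rows as looks, but the text names only the month-6 analysis.
- **Final design (section 2.8, Table 3).** Median PFS 4 against 8 months (HR 0.50), with "α=0.025 (two-sided), β=0.2, and at least 154 subjects with 77 subjects each group are required".
- **Treatment timing (sections 2.2 and 2.3).** Vaccine follows one week of radiotherapy and a one-week gap. A course lasts 5 months, with boosters at weeks 12 and 20. Section 2.2 adds: "Peptide vaccine therapy requires an 8-week preparation period for the preparation of the peptide vaccine, during which patients continue to maintain standard treatment".

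**The concern.** A decision that can end recruitment is tied to a calendar date at which, by the plan's own projection, almost no primary-endpoint information exists. Few vaccine patients will be far into the 5-month course by then. An effective vaccine could be dropped because of noise, and an ineffective one could look as good as the design hypothesis. The stated 80% power at alpha 0.025 also belongs to a trial without such a decision. Once the decision is real, at least one of those two properties changes, depending on how the look is used.

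**Working it through.** **Inputs.** Medians 4 and 8 months, uniform accrual over 24 months, 36 months in total, 1:1 allocation, 77 per arm, two-sided alpha 0.025 (critical value 2.241) and loss 0.10 (all section 2.8 and Tables 2 and 3). The article gives no time unit for the loss.

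**Step 1: reproduce the plan.** With exponential PFS and a loss of 10% per month:

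| Month | Recomputed events | Table 2 |
|---|---|---|
| 6 | 6.2 + 3.5 = 9.7 | 6.2 + 3.5 = 9.7 |
| 36 | 47.6 + 34.0 = 81.6 | 47.7 + 33.9 = 81.6 |

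A Lakatos log-rank calculation at N = 153 gives power 0.8028, which is Table 3's figure. That calculation is fixed-sample, with no interim. Of the loss rates tried, only 10% per month reproduces the tables.

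**Step 2: information and follow-up at month 6.**
- Information fraction: 9.7 / 81.6 = 11.9%.
- Mean follow-up: (35.6 + 41.1) / (19.2 + 19.3) = 76.7 / 38.5 = 2.0 months.
- Vaccine arm alone: 41.1 / 19.3 = 2.1 months, against a 5-month course.

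**Step 3: what 9.7 events can show.** SE(log HR) = 2/√9.7 = 0.64. The expected z at HR 0.5 is √(9.7/4) × ln 2 = 1.079.
- Power at two-sided 0.025: Φ(1.079 − 2.241) = 12%.
- Observed HR needed for significance: exp(−2.241 × 0.642) = 0.24.
- P(observed HR ≥ 1 given true 0.5) = Φ(−1.079) = 14%.
- P(observed HR ≤ 0.5 given true 1) = Φ(−1.079) = 14%.
- 95% CI around an observed HR of 0.5: 0.14 to 1.76.

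More generous readings change little. With loss of 10% overall instead of per month there are about 11.5 events and power is 14%. If all 40 patients had 6 months of follow-up there would be about 16 events and power of 19 to 20%.

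**Step 4: effect on the final design.** The interim and final z statistics have correlation √(9.7/81.6) = 0.345.
- Stop if the observed HR exceeds 1: power falls from 81.3% to 72.3%. Type I error is not inflated; on the benefit side it falls from 0.0126 to 0.0104.
- Continue only if significant at 0.025: about 88% of trials with a true HR of 0.5 stop.
- Efficacy claimable at both month 6 and the end, each at nominal 0.025: overall alpha 0.048.

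**Step 5: delayed vaccine effect.** Log-rank simulation of 40 patients at month 6, with HR 0.5 once the vaccine effect begins:

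| Start of vaccine effect | Correct direction | Power at 0.025 |
|---|---|---|
| At randomisation | 85% | 11% |
| Week 2 (radiotherapy plus gap) | 78% | 7% |
| Week 10 (8-week preparation after randomisation as well) | 57% | 2% |
| No effect at all | 49% favour vaccine | 1.3% |

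**Step 6: a later look.** Table 2 totals are 17.0 + 10.4 = 27.4 events at month 12 and 28.7 + 18.6 = 47.3 at month 18. By interpolation, 40 events fall at 12 + 6 × 12.6/19.9 = 15.8 months. The expected z there is √(40/4) × ln 2 = 2.19, so P(observed HR ≥ 1 given true 0.5) = 1.4%. Final power with the HR > 1 futility rule is 81.1%, against 81.3% with no look.

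**The case against.** This is a journal article. A decision threshold or stopping boundary may stand in the full protocol or SAP, so its absence here is not a finding. That is right, and the point does not rest on it: a boundary decides how 9.7 events are used but cannot add to them. The article itself fixes the timing and the purpose.

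Three stronger readings are tempting, and the article does not support them.

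- **The decision is close to chance.** The direction is right about 85% of the time at HR 0.5 with no delay, and 78% with a week-2 start. It nears chance (57%) only if peptide preparation follows randomisation, which the article does not state. Inclusion criterion 7 admits patients with sequencing data in hand or peptides already prepared, so some may start without that delay. For the same reason one cannot say that most follow-up precedes any vaccine effect.
- **Repeated looks inflate type I error.** The text names one interim, and its stated use is continued recruitment. A futility-only look causes no inflation. The figure of 0.048 applies only if efficacy can be claimed at month 6. Testing all six Table 2 rows would give about 0.083, but nothing says that they will be tested.
- **Patients average 3 months of follow-up at month 6.** That is time since entry under uniform accrual. Table 2's patient-months give 2.0.

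**Conclusion.** The point holds in this form: the month-6 look is placed where it cannot inform the recruitment decision assigned to it. It carries 12% of the planned information and 12% power at the design effect, with a 14% chance that an effective vaccine appears no better than control. Acting on it with the mildest rule considered takes the trial from 81% to about 72% power, so 154 patients would no longer deliver the stated 80%.

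These figures assume exponential PFS, HR 0.5 from randomisation, and the loss rate of 10% per month that reproduces Tables 2 and 3. A delayed vaccine effect makes the look weaker still; the more generous event counts in step 3 do not rescue it. The alpha figure is conditional on an efficacy claim at the interim. The matter should be settled before any recruitment decision relies on this look.

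**What to change.** 1. Make month 6 a safety and feasibility look, and remove the statement that its PFS result decides whether recruitment continues.
2. Place the single PFS-based look at about 40 events, counted in events rather than calendar time (months 15 to 16 on Table 2's assumptions).
3. State whether that look is for futility only or also for efficacy. For futility, a non-binding rule such as observed HR > 1 costs about 0.2 percentage points of power. If efficacy can be claimed, use an alpha-spending boundary (for example Lan-DeMets of O'Brien-Fleming type) that keeps overall two-sided alpha at 0.025.
4. State that the other Table 2 rows are projections, not tests.
5. State whether the 8-week preparation falls before or after randomisation, since this governs how much vaccine exposure any early look contains.

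**Cost.** Wording changes only, with no change in sample size. The first futility or efficacy decision comes about 9 to 10 months later. By then about 101 patients would be enrolled (interpolating Table 2 between 76.8 at month 12 and 115.2 at month 18), instead of about 40.

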### Statistical methods and data analysis

2.9

1. The results of this experiment mainly use statistical description methods. The measurement data lists the mean, standard deviation, median, maximum value, and minimum value, and the technical data and grade data list the frequency, rate, and confidence interval.2. All statistical analysis will be performed using SPSS software.3. Safety analysis: Mainly descriptive statistical analysis, analyzing adverse events, serious adverse events and adverse reactions of each group of people. Adverse reactions are defined as “definitely related/possibly related, unable to determine” related to this clinical trial.4. Survival Analysis: Progression-free survival (PFS), the primary endpoint of this study, will be analyzed based solely on data collected prior to cross-over, thereby preserving the integrity and statistical power of the comparison between neoantigen and placebo groups. The Kaplan-Meier method will be used to estimate the median PFS and calculate 95% confidence intervals. Group differences will be compared using the log-rank test. Overall survival (OS), as a secondary endpoint, will be estimated using Kaplan-Meier curves and log-rank tests. To account for potential bias introduced by the cross-over design, we will apply the rank preserving structural failure time (RPSFT) and two-stage methods, as well as inverse probability of censoring weighting (IPCW) to adjust for treatment switching. Additionally, adjusted OS analyses will be conducted by matching patients who cross over with comparable patients in the vaccine group based on key baseline factors (e.g., cancer type, age, performance status), using propensity score matching or multivariable Cox proportional hazards modeling. Sensitivity analyses will include intention-to-treat (ITT), per-protocol, and as-treated populations. Subjects will be stratified according to cancer type and first, second, and third-line treatment stages based on individual condition assessments, ensuring that these factors are appropriately considered in the analysis. Additionally, in the multivariable Cox proportional hazards model for both PFS and OS, cancer type will be included as a covariate, along with other relevant baseline factors, to control for potential confounding effects.5. Other Effectiveness analysis: Estimate the objective response rate (ORR), disease control rate (DCR) and other efficacy endpoints and improve the 95% confidence interval. The interval estimation uses the Clopper-Pearson method. The effect of lab correlates such as RT dose on clinical outcomes of response and time-to-event will be estimated using logistic regression and Cox mode respectively. The longitudinal data such as quality of life will be estimated using mixed-effect model.6. Tumor neoantigens response analysis: Neoantigen-specific responses are evaluated by ELISPOT, flow cytometry, and TCR-seq. Peptide–MHC tetramers enrich specific T cells for scRNA/TCR-seq analysis in PBMCs and tumor tissue (if available). TCR clonotype dynamics, ctDNA, and epitope spreading are monitored over time. IHC/mIHC is used to assess immune microenvironment changes when biopsy samples are available.

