Patients entering the control group’s conventional treatment (including radiotherapy) group will receive conventional treatment plus radiotherapy. Radiotherapy is divided into low-dose and high-dose (first phase); until disease progression occurs, patients can choose to “cross groups” and receive individual treatment. The second stage of treatment consists of tumor peptide vaccine plus radiotherapy (no harm from treatment in the early stage). Patients entering the intervention group ‘s individualized tumor peptide vaccine + conventional treatment (including radiotherapy) group will complete three precise radiotherapy sessions before initiating vaccination with the peptide vaccine. The peptide vaccine treatment will be carried out one week after the end of radiotherapy. The peptide vaccine treatment will last for 5 months. It is a course of treatment until the treatment discontinuation event specified in the protocol occurs. Subjects will continue to undergo post-treatment safety visits, survival follow-ups and tumor progression follow-ups after finishing treatment.

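### The additional matched OS analysis compares crossed-over controls with vaccine-arm patients, both vaccinated, so it cannot adjust for crossover or estimate vaccine versus no vaccine

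*Protocol article*

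**What the plan says.** Section 2.9, item 4 sets out the OS analysis in layers. The main analysis is conventional: "Overall survival (OS), as a secondary endpoint, will be estimated using Kaplan-Meier curves and log-rank tests". Crossover is then addressed: "To account for potential bias introduced by the cross-over design, we will apply the rank preserving structural failure time (RPSFT) and two-stage methods", with IPCW named as well. A further layer follows, in which "adjusted OS analyses will be conducted by matching patients who cross over with comparable patients in the vaccine group based on key baseline factors". The examples of such factors are cancer type, age and performance status, and the tools are given as "using propensity score matching or multivariable Cox proportional hazards modeling". ITT, per-protocol and as-treated populations are listed for sensitivity analyses.

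Section 2.2 defines the crossover patients. Crossover "will be permitted only for patients in the control group who demonstrate radiologically confirmed disease progression", subject to conditions "including an ECOG performance status of ≤2, absence of Grade ≥3 adverse events, and adequate hematologic, hepatic, and renal function". Patients may choose whether to cross. On what they then receive, Section 2.2 states: "The second stage of treatment consists of tumor peptide vaccine plus radiotherapy". Vaccine-arm patients start the vaccine one week after radiotherapy, with no requirement to have progressed.

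**The concern.** The sentence comes directly after the switching methods and calls its result an adjusted OS analysis, so a reader will take it as a correction for crossover. Such a correction has to recover what would have happened to controls without the vaccine. This comparison contains nobody without the vaccine, and controls who never cross over are left out of it.

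At stake is a prespecified result on a secondary endpoint that would be reported beside RPSFT, two-stage and IPCW. It could disagree with them for reasons unrelated to the vaccine. Section 3.2 presents the crossover arm as a way to evaluate vaccine efficacy further, so the result may well be read that way.

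**Working it through.** **Step 1: the two groups side by side.**

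| | Crossed-over controls | Vaccine arm |
|---|---|---|
| Receives vaccine plus radiotherapy | Yes, after progression | Yes, from the start of study treatment |
| Must have progressed | Yes | No |
| Must be alive and meet fitness criteria at a later date | Yes | No |
| Chooses to enter the group | Yes | No, randomised |

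The first row removes the unvaccinated comparator. The other rows describe selection after randomisation, which matching or Cox adjustment on baseline factors cannot correct.

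**Step 2: inputs.** From Section 2.8: control median PFS 4 months, 77 per group, accrual 24 months, total 36 months, loss 0.10. The document gives no post-progression survival, crossover uptake or share of PFS events that are deaths. Those are assumptions here.

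The sizing is not in dispute. It was reproduced to see how the loss rate was used. For HR 0.50, two-sided α = 0.025 and 80% power, the Schoenfeld formula gives 4(2.241 + 0.842)²/(ln 0.5)² = 79.1, so 80 events. Table 2 gives 47.7 + 33.9 = 81.6. Reading the loss as 10% per month gives event probabilities of 61.9% and 44.2%, against 61.9% and 44.0% in Table 2, and power of 0.813. The loss was therefore applied as a monthly rate.

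**Step 3: hand check with no vaccine effect.** Assume exponential times, a post-progression median of 6 months, and 15% of first events being deaths.

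- Mean time to first event: 4/ln 2 = 5.77 months. Mean time after progression: 6/ln 2 = 8.66 months.
- Vaccine arm, mean OS: 5.77 + 0.85 × 8.66 = 13.13 months.
- Crossover patients counted from randomisation (all progressed alive): 5.77 + 8.66 = 14.43 months.
- Crossover patients counted from crossover: 8.66 months.

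The ratio of crossover to vaccine-arm means is a rough guide to the HR of vaccine arm versus crossover. It is 14.43/13.13 = 1.10 from randomisation and 8.66/13.13 = 0.66 from crossover. Neither is 1, although the vaccine does nothing.

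**Step 4: large-sample simulation** (100,000 per arm, the same assumptions, about 59% of controls crossing over, OS censored at 36 months). The first figure in each range is without an unmeasured frailty. The second has a frailty that also favours crossover.

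| Vaccine hazard multiplier | OS HR if nobody crossed over | ITT OS HR | Vaccine arm v crossover, both from randomisation | Vaccine arm v crossover, crossover patients from crossover |
|---|---|---|---|---|
| 1.0 | 1.00 | 1.00 | 1.13–1.27 | 0.63–0.72 |
| 0.7 | 0.63–0.70 | 0.77–0.81 | 0.95–1.11 | 0.61–0.71 |
| 0.5 | 0.41–0.49 | 0.62–0.67 | 0.83–1.00 | 0.58–0.69 |

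The last column hardly moves whether the vaccine works or not, so its agreement with the truth in the middle row is chance. In both rows with a real effect, the randomisation clock lies further from the no-crossover HR than unadjusted ITT does.

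**Step 5: simulation at trial size** (77 per arm, cut at month 36, 10% of first events deaths, 70% uptake, post-progression median 6 months).

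- No vaccine effect, crossover clock: HR about 0.54. The range is 0.43 to 0.67 as the post-progression median varies over 4 to 10 months and uptake over 50 to 90%.
- No vaccine effect, randomisation clock: HR 1.02 to 1.07 over repeated runs, or 1.29 to 1.31 if crossover patients wait 10 weeks after progression. The 10 weeks are 8 of preparation, 1 of radiotherapy and a 1-week interval, and assume that preparation starts only at progression.
- Survival truly lengthened 1.5-fold (HR 0.57 versus never vaccinated), randomisation clock: HR 0.86 to 0.87, or 1.05 with the wait.

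**The case against.** The strongest reply concerns weight. This is an extra analysis of a secondary endpoint. The primary PFS comparison uses only data from before crossover, and OS already has an ITT analysis and three recognised switching methods. No sample size, stopping rule or success criterion in the document uses the matched result. All of that stands, and it limits the point to one sentence.

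A reader might also infer that the analysis counts the two groups from different time origins and so manufactures a vaccine benefit. The document does not support that as a statement of fact. It names no clock, and an article may leave that detail to the full protocol or SAP. With the usual OS origin, randomisation, the null HR at trial size is close to 1 when there is no wait, so no false benefit appears. The error then is to hide a real benefit.

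The figures also depend on the assumptions. With the crossover clock and no vaccine effect, 69 to 76% of simulated trials were significant at two-sided 0.025 without loss to follow-up. With 10% monthly loss it was 54 to 58%. That loss also moved the randomisation-clock null HR in one set of runs from 1.05 to 0.92. The direction under the crossover clock survives, but the precision does not.

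None of this rescues the contrast. Whichever clock is chosen, both groups are vaccinated and one is selected on later events.

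**Conclusion.** The point holds for the matched analysis alone. As worded, it compares early with deferred vaccination in selected survivors, and no time origin turns that into vaccine versus no vaccine. This conclusion follows from the stated groups and needs no simulation.

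The sizes are illustrative. They rest on an assumed post-progression median of 6 months, about 60 to 70% uptake, 10 to 15% of first events being deaths, and exponential times. On those terms a null vaccine gives an HR of about 0.5 to 0.7 with the crossover clock. A true HR of about 0.57 appears as about 0.86 to 1.05 with the randomisation clock.

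A reader might infer that the trial's OS evidence as a whole is compromised. It is not: primary PFS, ITT OS, RPSFT, two-stage and IPCW do not depend on this comparison. The sentence should be fixed, but the trial's main conclusion does not hang on it.

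**What to change.** In Section 2.9, item 4, delete the matching or Cox comparison of crossover patients with the vaccine group as an OS adjustment. Alternatively, keep it under a different label: a descriptive comparison of early with deferred vaccination, with its time origin stated and a note that it supports no claim of vaccine efficacy. OS should rest on the randomised ITT comparison plus the RPSFT, two-stage and IPCW analyses already named.

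Do not replace it with a match of crossover patients to controls who progressed but did not cross over, timed from progression. Any wait before crossover gives the crossover patients guaranteed survival. With no vaccine effect and a 10-week wait, that match gave an HR of 0.47 for crossover versus non-crossover, significant in 68% of simulated trials. The two-stage and IPCW methods already draw on the control-arm information.

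The cost is one reworded or deleted sentence. No new data are needed, and neither the sample size nor patient care changes.
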